#### Randomisation and allocation concealment

Following the application of sterile drapes to the participant, but immediately prior to skin incision, participants will receive one of the following interventions:

Group A: inflation of the tourniquet applied around the participant’s thigh or calf of the operative limb.Group B: inflation of the tourniquet applied around the pillow.

Consented participants will be randomised 1:1 to the intervention (Group A) or the control group (Group B) using a validated online computer-generated sequence via Castor’s Electronic Data Capture (EDC) system, managed by UHCW NHS Trust and will be stratified by study centre.^23^ The randomisation sequence will be created using varying block sizes of 4 and 6 to minimise predictability.

To maintain allocation concealment, randomisation will be performed within 24 hours of the participant’s surgery by an operating department practitioner or another appropriately trained member of the research team. Only the operating department practitioner responsible for implementing the allocation will be informed of the randomisation outcome and is not permitted to disclose it to the participant or any member of the clinical team. The allocation sequence will not be accessible to staff involved in identifying or approaching patients for participation.

#### Inflation procedures

The tourniquet will be inflated to a pressure of 70–130 mm Hg above the participant’s systolic blood pressure, in accordance with BOAST guidance.^22^ Participants will undergo routine ankle fracture fixation using the standard operative technique of the surgeon. The earliest opportunity at which the tourniquet may be deflated is on completion of fracture fixation; however, it may remain inflated beyond this point at the surgeon’s discretion. If the ischaemic tourniquet time exceeds 120 min, the tourniquet must be deflated for a minimum of 10 min. Reinflation is permitted only following a thorough clinical assessment of the relative risks and benefits by the operating surgeon.

#### Clinical outcomes and time points

As this is a feasibility study, the primary outcomes include recruitment and retention rates, data completeness for clinical and patient-reported outcomes, success of blinding and adherence to allocated intervention. Clinical and patient-reported outcomes are not statistically powered and will be summarised descriptively to inform the decision on progression to a future definitive trial.

The secondary outcomes below are also exploratory and not statistically powered. These are intended to inform the selection of outcomes and required sample size for any future definitive trial. They will also provide information on the feasibility of outcome data collection, including questionnaire acceptability and data completeness over follow-up. Participants will receive reminders via phone and/or email to complete outcome questionnaires.

Postoperative pain will be assessed at multiple time points, evaluating various attributes, including duration, intensity, location and pain characteristics (eg, neuropathic and nociceptive). Pain location and character will be measured at baseline (preoperatively), 24 hours and 3 months postoperatively using the painDETECT questionnaire.^24^ Pain intensity at the ankle, calf and thigh regions will be assessed using an 11-point Numerical Rating Scale, where 0 represents ‘no pain’ and 10 represents ‘worst possible pain’,^25^ at 24 hours, 3 weeks and 3 months postoperatively. Total inpatient analgesic consumption and medications prescribed or recommended at discharge will be recorded. Data on analgesia use (drug name, dosage, route and timing) will be collected for 3 weeks from surgery.Surgeon-reported quality of the surgical field will be evaluated using a 5-point Likert scale (‘very dissatisfied’, ‘dissatisfied’, ‘unsure’, ‘satisfied’ and ‘very satisfied’).Intraoperative blood loss will be quantified by calculating the difference in weight of the surgical swabs before the skin incision and after wound closure, reported in grams. The volume of fluid collected in the suction container will also be measured. To calculate the volume of blood loss, the volume of any irrigation or other fluids used during the procedure will be subtracted, with the final value reported in millilitres.The number of blood transfusions administered intraoperatively and postoperatively until discharge will be recorded, based on hospital records and reported as the number of units transfused.Intraoperative complications, including vascular, ligamentous, tendinous and neurological injuries, will be captured via a surgeon-completed questionnaire.Postoperative complications will be captured using a self-reported questionnaire, sent to participants at 3 months postoperatively (via email or post). This will include wound complications, surgical site infections, deep vein thrombosis, pulmonary embolism and reoperation (planned and unplanned). Responses will be cross-checked with hospital records, which will also be reviewed to identify additional complications such as fracture non-union, mal-union and neurovascular injury.Tourniquet-related skin injuries, including burns, contusions and pressure sores, will be assessed based on clinical documentation from the operating department practitioners who routinely inspect the tourniquet site before and after its use.Awareness of tourniquet use will be assessed by asking participants and surgeons to complete a short questionnaire on the day of surgery and at 3 months (eg, ‘*Do you think a tourniquet was used during the operation?’*).Procedure duration will be recorded in minutes, from the time of skin incision to completion of wound closure for the ankle fracture fixation procedure.The Olerud-Molander Ankle Score is a validated 9-item patient-reported outcome measure used to assess functional recovery after ankle injuries.^26^ It assesses pain, functional activities and symptoms such as stiffness and swelling, with a total score ranging from 0 to 100 (higher scores indicate better outcomes).HRQoL will be assessed using the EuroQol-5D-5L questionnaire, a self-completed instrument comprising a five-dimensional health status classification system and a visual analogue scale.^27^

Table 2 details the time points at which each outcome will be assessed.

**Table 2 T2:** Time points for assessment of outcomes

Timing	Baseline (retrospective pre injury score)	On day of surgery (pre operatively)	On day of surgery (post operatively)	24 hours post operatively	2 weeks post operatively	3 weeks post operatively	3 months post operatively
Outcome							
Pain (painDETECT)	✓			✓			✓
Pain (NRS)				✓		✓	✓
Analgesia use	✓		✓			✓	
Surgical field of view			✓				
Blood loss			✓				
Blood transfusions			✓		✓		
Length of procedure			✓				
Skin assessment		✓	✓				
Awareness of tourniquet use			✓				✓
EQ-5D-5L	✓					✓	✓
OMAS	✓					✓	✓
Intraoperative complications			✓				
Postoperative complications							✓

EQ-5D-5L, EuroQol-5D-5L; NRS, Numerical Rating Scale; OMAS, Olerud-Molander Ankle Score .

#### Statistical analysis

Categorical variables will be summarised as frequencies and percentages and analysed using χ^2^ or Fisher’s exact tests. Parametric data will be reported using mean and SD and analysed using t-tests. Non-parametric data will be reported as median and IQR and analysed using the Mann-Whitney U test. Effect estimates will be presented with 95% CIs. Given the feasibility design, analyses of clinical outcomes are exploratory and not intended to support definitive inference regarding the effectiveness of the interventions. Statistical tests (p values) will be reported descriptively and interpreted cautiously as the study is not powered to detect between-group differences in clinical outcomes.

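### Only unadjusted two-group tests are named, although allocation is stratified by centre and baseline scores are collected: valid, but possibly less precise than it could be, and short of what a baseline-adjusted definitive trial needs for planning

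*Protocol article*

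**What the plan says.** All places are in the protocol article.

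- **Statistical analysis.** For continuous data: "Parametric data will be reported using mean and SD and analysed using t-tests". Non-parametric data get the median, IQR and Mann-Whitney U. For categorical data: "Categorical variables will be summarised as frequencies and percentages and analysed using χ^2^ or Fisher’s exact tests". The section adds: "Effect estimates will be presented with 95% CIs". No covariate or stratified analysis is mentioned. Clinical comparisons are declared exploratory and unpowered.
- **Randomisation and allocation concealment.** Allocation "will be stratified by study centre", with two centres and blocks of 4 and 6.
- **Table 2.** Under the column "Baseline (retrospective pre injury score", ticks appear for painDETECT, analgesia use, EQ-5D-5L and OMAS. Pain NRS, blood loss, surgical field and length of procedure have none.
- **Clinical outcomes and time points, on painDETECT.** "Pain location and character will be measured at baseline (preoperatively), 24 hours and 3 months postoperatively using the painDETECT questionnaire".
- **The same section, on the surgical field.** "Surgeon-reported quality of the surgical field will be evaluated using a 5-point Likert scale". No test is assigned to it by name.
- **Objectives.** One aim is to obtain estimates that inform the definitive trial's sample size. The Introduction says that size is unknown.

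**The concern.** Centre stratification balances the arms within each hospital. A t-test that ignores centre still counts the between-hospital difference as noise. In the same way, an unadjusted comparison of 3-month OMAS leaves in the variance whatever part the baseline score explains. Both cost precision when the factor is prognostic, and neither costs anything to collect because the data are already planned.

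The more practical stake is the definitive trial. If it is to be analysed with baseline adjustment, its sample size rests on the residual SD, or equivalently on the raw SD and the baseline-outcome correlation. The planned output of means and SDs by arm does not include that correlation.

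Two smaller matters belong here. The surgical-field scale has five ordered levels, and the analysis text leaves open whether it counts as categorical (χ², which ignores the order) or non-parametric (Mann-Whitney, which uses it). The painDETECT baseline, a candidate covariate, is described as preoperative in the text but sits in Table 2 under a recalled pre-injury heading, with the separate preoperative column blank.

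**Working it through.** The article states no SD, effect size, correlation or centre effect, so there is no figure to reproduce. Inputs from the article: N = 50 (the maximum), 1:1 allocation so n = 25 per arm, two centres, blocks of 4 and 6, 95% intervals. Assumed: r from 0 to 0.7; the share of variance explained by centre (R²) from 0 to 0.10; a 30/20 split between centres in the simulations.

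**1. Unadjusted half-width, in SD units.** t(0.975, 48) × √(2/25) = 2.0106 × 0.2828 = 0.569.

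**2. Adjusted for centre and baseline.** t(0.975, 46) × √[(2/25)(1 − r²)(47/45)]. The factor 47/45 is the average cost of chance imbalance in two covariates, and centre is given no effect here. At r = 0 this is 2.0129 × √0.08356 = 0.582; other rows multiply by √(1 − r²).

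| r | Half-width | Change from 0.569 | Residual SD / raw SD |
|---|---|---|---|
| 0 | 0.582 | +2.3% | 1.000 |
| 0.2 | 0.570 | +0.2% | 0.980 |
| 0.3 | 0.555 | −2.4% | 0.954 |
| 0.5 | 0.504 | −11.4% | 0.866 |
| 0.7 | 0.416 | −26.9% | 0.714 |

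If fewer patients are analysed, the cost at r = 0 rises to 3.0% (N = 40) or 4.3% (N = 30).

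**3. Centre only, for outcomes without a baseline.** t(0.975, 47) × √[(2/25)(1 − R²)]. The change is +0.1% at R² = 0, −1.0% at 0.02, −2.5% at 0.05 and −5.1% at 0.10.

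**4. Validity.** In a simulation with centre-stratified blocks of 4 and 6 (8,000 runs per scenario, r of 0, 0.3, 0.5 and 0.7, centre shift of 0 or 0.5 SD), the unadjusted interval covered 94.3% to 95.8% of the time. Adjusted width over unadjusted width was 1.01 with nothing prognostic, 0.97 at r = 0.3, 0.88 at 0.5 and 0.72 at 0.7. With a 0.5 SD centre shift these became 0.98, 0.94, 0.85 and 0.70. With an assumed 1 SD shift and no baseline, unadjusted coverage rose to about 96.7%, and adjusting for centre narrowed the interval by about 10%. The error is therefore towards caution.

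**5. Consequence for the definitive trial.** Illustration with an assumed effect of 0.3 SD and 90% power: n per arm = 2(1.960 + 1.282)² / 0.09 = 233.5, so 234 with the raw SD. Multiplying 233.5 by (1 − r²) gives 213 at r = 0.3, 176 at 0.5 and 120 at 0.7.

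**6. Sampling error in the SD itself.** With 48 degrees of freedom, the χ² interval for the SD is 0.834 to 1.249 times the estimate, which is 163 to 365 per arm on the same illustration.

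**7. Surgical-field scale.** Assumed control distribution 8/20/20/36/16% over the five levels, 25 per arm, proportional odds. At an odds ratio of 3, simulated power is about 30% for χ² on the 2×5 table and 55% for Mann-Whitney; at 4, about 49% and 75%. This shows only what is lost if the scale is treated as unordered.

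**The case against.** The planned tests are valid, the primary outcomes are feasibility measures, and no feasibility conclusion turns on t-test against regression. The baselines are, by the Table 2 heading, mostly recalled pre-injury scores, whose correlation with outcome after a fracture may be low enough for adjustment to gain nothing. Several outcomes have no baseline at all. A separate analysis plan that is not shown may already specify adjusted models. All of this stands, and it limits the weight of the point.

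Three stronger readings are tempting, and the article supports none of them.

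- **The definitive trial will be given the wrong SD.** No text says which SD will be carried forward or how that trial will be analysed. The raw SD is correct for an unadjusted comparison and conservative for an adjusted one, and the residual SD can be recovered from the same data as raw SD × √(1 − r²). At r = 0.3, raw against residual (234 against 213 per arm) matters less than the sampling error in the SD (163 to 365).
- **The intervals are wider than needed, full stop.** That depends on a correlation or centre effect that the article does not give.
- **The surgical-field scale will be tested by χ².** It is not assigned to χ²; Mann-Whitney is also in the plan.

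On painDETECT, the text may describe when the form is completed and Table 2 the period recalled. That reading is possible, so this is an ambiguity to resolve rather than a proven contradiction.

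What survives is that the named methods use neither the stratification factor nor the baselines, and that adding them serves a stated objective almost free of charge.

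**Conclusion.** The point holds as a modest, inexpensive improvement rather than an error in the planned inference. For OMAS, EQ-5D-5L and painDETECT, adjustment is worth having if r is about 0.3 or more and material from about 0.5 (11% narrower). At 0.2 or below it brings nothing. For outcomes without a baseline, centre adjustment changes the width by +0.1% to −5.1% over the R² range examined. For planning, the raw SD should not stand alone if a baseline-adjusted definitive trial is in view. These sizes rest on assumed correlations and centre effects, 50 analysed patients, and roughly normal outcomes with a linear baseline relation.

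**What to change.** Add to the Statistical analysis section or the analysis plan:

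1. Estimate differences in OMAS, EQ-5D-5L and painDETECT by linear regression of the follow-up score on arm, centre and the same measure's baseline.
2. Estimate differences in continuous outcomes without a baseline by linear regression on arm and centre.
3. Report adjusted differences with 95% confidence intervals. For each measure with a baseline, give the residual SD and the baseline-outcome correlation beside the raw SD.
4. State that the five-level surgical-field scale will be analysed by a rank or ordinal method, such as a proportional-odds model with arm and centre, and not by χ².
5. Check on the case report form whether the painDETECT baseline refers to preoperative or pre-injury pain, and bring the outcome text and Table 2 into line before using it as a covariate.

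The cost is wording and slightly more analysis work, with no new data. If neither centre nor baseline is prognostic, the loss is at most about 2% of interval width with 50 analysed patients, and 3% with 40.

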### Integrated qualitative interview study

#### Objectives

Explore patients’ experiences of participating in the feasibility trial.Explore surgeons’ experiences of participating in the feasibility trial.Explore potential barriers and enablers to patients’ participation and retention.Explore potential barriers and enablers to surgeons’ participation.Explore whether blinding influenced surgeons’ typical practice.Explore the causes of unblinding of patients.Explore the causes of unblinding of surgeons.Understand reasons for any protocol deviation and data incompleteness by surgeons and identify changes to enhance recruitment.Understand reasons for data incompleteness and loss to follow-up of patients and identify changes to enhance recruitment and follow-up.Explore patients’ views on the participant information materials and potential areas for improvement.

#### Reporting

The study will be reported in accordance with the Consolidated Criteria for Reporting Qualitative Research (COREQ).^28^

#### Study design and eligibility criteria

This is a qualitative study involving one-to-one interviews with patients and trauma and orthopaedic surgeons. Patient eligibility criteria match those in the feasibility RCT (table 1). Eligibility criteria for trauma and orthopaedic surgeons are outlined in table 3. Participants will be recruited from the same sites as the feasibility RCT.

**Table 3 T3:** Study eligibility criteria for trauma and orthopaedic surgeons

Inclusion criteria	Exclusion criteria
Aged 18 years and over. Consultant trauma and orthopaedic surgeons who participated or declined to participate in the feasibility RCT. Patients who participated or declined to participate in the feasibility RCT. Ability to provide informed consent.	Unable to understand and speak English

RCT, randomised controlled trial.

#### Participant identification, recruitment and consent

Identification of eligible patients will follow the same process as described in the feasibility RCT methods section. The consent form for the feasibility RCT includes an explicit request for participants’ voluntary permission to be contacted about this qualitative interview study. In the original protocol, patients who provided consent to being contacted could only be approached by telephone or email by a member of the research team after completing their participation in the RCT, to confirm their interest in taking part in the qualitative interview study. Following a protocol amendment (V.5.1, 1 December 2025) patients could be approached 1 month after trial enrolment. Also, patients who declined to participate in the feasibility RCT will have been asked at that time whether they would be willing to participate in this qualitative interview study. In both scenarios, patients will be provided with a participant information sheet and a separate consent form specific to this qualitative interview study. They will also be given the opportunity to ask questions and contact details for the research team will be provided.

Consultant trauma and orthopaedic surgeons based at their participating hospitals will be approached in person or remotely (via phone or email) to explore their interest in being interviewed. The screening log from the feasibility RCT will be reviewed to identify surgeons who took part in or declined involvement in the trial.

Recruitment for both patients and surgeons will require either signed written consent or return of a completed consent form via email, with digital/electronic signatures accepted.

#### Sample size

Approximately 12 trauma and orthopaedic surgeons and 12 patients will be recruited for this study. This sample size is anticipated to be sufficient to achieve data saturation in relation to the study’s objectives.

#### Sampling technique

Purposive sampling will be employed to ensure a diverse range of participant characteristics.

Factors which will be considered during sampling of patients include age, sex, ethnicity and socioeconomic status. Socioeconomic status will be inferred using the Index of Multiple Deprivation, based on the participant’s home postcode.

For trauma and orthopaedic surgeons, sampling will consider ethnicity, sex, years of clinical experience and subspecialty (eg, foot and ankle or trauma).

#### Data collection and analysis

Semistructured interviews will be conducted by surgical researchers, either face-to-face or virtually over Microsoft Teams, depending on participants’ preference. Interviews will be audio-recorded using an encrypted digital voice recorder for in-person interviews or via Microsoft Teams for online interviews. Recordings will be transcribed verbatim, checked for accuracy and anonymised. Transcription will be conducted either by an approved commercial company or through the automated transcription function available in Microsoft Teams. Data will be managed using NVivo qualitative analysis software and analysed using thematic analysis.^29^ Using an inductive approach, data of similar meaning will be grouped into codes, which will then be organised into broader categories by comparing within and across the codes. Overarching themes will be developed to encapsulate these categories. Themes will be explored to ensure they are robust and then explored in relation to relevant theoretical literature. Trustworthiness of the analysis will be achieved through several strategies including peer debriefing and maintenance of a reflexive diary by the lead researcher.^30 31^

### Data management

Each participant will be assigned a unique trial identification number. All RCT data collected will be entered into a secure trial database hosted on Castor’s EDC system.^23^ Identifiable participant information will be stored separately in a locked filing cabinet and linked to the trial data only via the unique trial identification number. Trial records will be audited by the quality assurance team at the Warwick Clinical Trials Unit, in accordance with standard operating procedures.

Audio recording data from the integrated qualitative interview study will be temporarily stored on the University of Warwick OneDrive for Business and a secure link enabling access to these files will be provided to the approved commercial company for transcription. On completion of transcription, data will be deleted from OneDrive for Business.

### Trial oversight

The Trial Management Group (TMG), comprising members of the research team responsible for the day-to-day conduct of the study, will meet monthly. As this is a small feasibility study, there is no independent trial steering committee or data monitoring committee. Adverse events and serious adverse events will be monitored by members of the principal investigator’s trial team. The trial may be stopped prematurely if mandated by the research ethics committee, if a significant and unforeseen safety concern arises or in the event of funding withdrawal. Any proposed amendments to the study protocol will first be reviewed by the TMG and, subject to approval, will be submitted to the trial sponsor, funding body and local research ethics committee for further review and approval. Approved amendments will be communicated to the relevant parties.

### Patient and public involvement

To inform the development of this research and support the grant application, this project was discussed with 10 patients who had undergone ankle fixation surgery. Patients attended an online virtual focus group in December 2020 to discuss their views on tourniquet use in ankle fracture surgery. They said this research project was important to carry out and their views helped shape the design of the research project.

Further engagement work with patients, surgeons and operating department practitioners was completed in preparation for this feasibility trial (REC 23/EE/0214), after the grant was awarded. This included four focus groups involving 20 patients who underwent ankle fracture fixation surgery, completed in 2024. These discussions helped ensure the most important outcomes for patients would be included in this trial. Two patients agreed to act as members for this study’s patient and public involvement group and help contribute to the delivery, management, interpretation and dissemination of this study’s findings.

To inform trial participant eligibility criteria and refine key parameters of tourniquet use, five trauma and orthopaedic surgeons and two anaesthetists were consulted via nominal group technique research. Consensus was obtained on key trial parameters, including patient eligibility criteria, timing of tourniquet inflation and deflation, tourniquet pressures to be used and blinding methodology.

Lastly, four operating department practitioners were interviewed about their role in controlling the tourniquet machine. These interviews helped explore potential blinding methods, identified challenges to maintaining blinding for both patients and surgeons and suggested possible solutions to address these issues. These discussions helped shape this study’s blinding method.

